### Measures

#### Primary outcome measures

PCBD will be assessed with the Traumatic Grief Inventory-Self Report (TGI-SR).^43^ The TGI-SR consists of 18 items on a 5-point Likert scale ranging from 1=never to 5=always. Four items tapping disturbed grief criteria according to the 11th edition of the International Classification of Diseases were added.^44^ An example of an item is: ‘I found it difficult to trust others’. The instruction of the original questionnaire was altered from referring to ‘the death of your loved one’ to ‘the death of your loved one(s) due to a traffic accident’. Psychometric properties of the TGI-SR are adequate.^43 45^ Participants are considered to meet criteria for DSM-5 PCBD^4^ when they score at least 3 (‘sometimes’) on at least 1 criterion B symptom (Item 1, item 2, item 3 and item 14), at least six criteria C symptoms (item 4 up to 11, and item 15 up to 18) and the criterion D symptom (item 13).

PTSD will be assessed with the PTSD checklist for DSM-5 (PCL-5)^46^ (Dutch version^47^). Participants rate how often they were bothered by each symptom (eg, ‘In the past month, how much were you bothered by trouble remembering important parts of the accident?’) on 5-point Likert scales (0=not at all and 4=extremely). The instruction and the items of the original questionnaire are altered from referring to the ‘stressful event’ to the ‘the death of your loved one(s) due to a traffic accident’. The PCL-5 has shown to be reliable and valid.^46^ Participants meet the criteria for DSM-5 PTSD^4^ when they score at least 2 (‘Moderately’) on 1 criterion B item (items 1–5), 1 criterion C item (items 6–7), 2 criterion D items (items 8–14), and 2 criterion E items (items 15–20).

Depression symptom levels are assessed with the depression subscale of the HADS-D.^48^ The HADS-D consists of seven items (eg, ‘I still enjoy the thing I used to do’) rated on 4-point scores ranging from 0 (eg, ‘Hardly at all’) through 3 (eg, ‘Definitely as much’). The Dutch HADS-D is a reliable and valid screening tool for depression.^49^ A cut-off score of ≥8 is used as indicator for clinically relevant depression.^48^

#### Secondary outcome measures

Negative grief-related cognitions are assessed with 18 items from the Grief Cognitions Questionnaire.^14^ Participants are asked to rate their agreement with each item (eg, ‘Since [–] is dead, I feel less worthy’) on 6-point scales varying from 0=disagree strongly through 5=agree strongly. The psychometric properties have been positively evaluated in prior research.^14^

Avoidance is measured with the Depressive and Anxious Avoidance in Prolonged Grief Questionnaire (DAAPGQ).^50^ The depressive avoidance subscale consists of 5 items (eg, ‘Since [–] is dead, I do much less of the things that I used to enjoy.’) and the anxious avoidance subscale consists of 4 items (eg, ‘I avoid to dwell on painful thoughts and memories connected to his/her death.’). Participants answer each item on an 8-point scale with 0=not at all true for me, and 7=completely true for me. The DAAPGQ has adequate psychometric properties.^50^

State anger is assessed with the 15-item state anger subscale of the State-Trait Anger Expression Inventory-2 (STAXI-2)^51^ (Dutch version:^52^). Participants are asked to rate on 4-point Likert scales (1=not at all and 4=extremely) how angry they feel right now (eg, ‘I feel annoyed’). The STAXI-2 is a valid and reliable measure to assess state anger.^52^

A sense of unrealness is measured with the 5-item Experienced Unrealness Scale.^17^ Participants are asked to rate their agreement with each item (eg, ‘I still can hardly imagine that [–] will never be here again’) on 8-point scales (0=not at all true for me 7=completely true for me). This instrument demonstrated adequate psychometric properties.^17^

Self-efficacy is assessed with the General Self-Efficacy Scale (GSES).^53^ The GSES is a 10-item measure. Participants are asked to rate their agreement with each item (eg, ‘I can solve most problems if I invest the necessary effort.’) on a 4-point scale (1=completely not true, 4=completely true). The GSES has shown excellent reliability and validity.^53^

Quality of the therapeutic alliance is measured with the 12-item Work Alliance Inventory-Short Form, Client Version and Therapist Version after session 4 (WAI-SF)^54^ (Dutch version^55^) The WAI-SF consists of 12 items (eg, Client version: ‘We agree on what is important for me to work on’, Therapist Version: ‘We are working towards mutually agreed on goals.’) that are rated on 5-point scales (1=never and 5=always). Higher total scores indicate a higher quality of the therapeutic alliance as perceived by the participant and therapist. The WAI-SF is a reliable and valid assessment tool.^56^

#### Other measures

Background characteristics (ie, gender, age and educational level, kinship to the deceased and time since loss) and accident-related stressors (ie, single vs multiple loss, witnessed the accident and status of legal trial) will be assessed with single items.

Participants are allowed to receive other forms of psychosocial, instrumental or legal support during participation in the trial. Using a single question, we will assess whether the participants received other forms of psychosocial professional support. The following question will be used: ‘During the past 12 weeks/8 weeks (for T2 and T3, respectively) did you receive additional psychological professional support from a psychologist, therapist or psychiatrist other than the (online) therapist from the TrafVic-study?’ We will also include two dichotomous items (yes/no) at T1 to assess psychological support received prior to participation in the study, namely: ‘Did you ever receive support from a psychologist, therapist or psychiatrist, for your own emotional/mental problems, prior to the loss of your loved one due to a traffic accident?’ and ‘Did you ever receive support from a psychologist, therapist or psychiatrist, for your own emotional/mental problems, related to the loss of your loved one due to a traffic accident?’

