## Methods and analysis

### Design

A two-arm (online CBT vs waiting list) multicentre open label parallel randomised controlled trial (RCT) will be conducted. Randomisation will take place after the participant is screened for eligibility-based inclusion criteria (described below). A random number generator (www.random.org) will be used by a blinded independent researcher, to perform the blocking randomisation procedure. An allocation ratio of 1:1 will be applied.

Participants allocated to the online CBT condition receive treatment within 1 week after allocation. All participants will be asked to fill in questionnaires (described below) at baseline (T1), 12 weeks postallocation (T2 for the intervention condition and T1a for waitlist controls) and 20 weeks postallocation (T3 for the intervention condition and T1b for waitlist controls). For participants in the waiting list control group, at the end of the 20-week waiting period after which they will receive online CBT, they will be asked to fill in T2 and T3 12 and 20 weeks after starting treatment, respectively (see figure 1). A link to online questionnaires will be sent to the participants by a non-blinded member of the research team at each time point. A waitlist control group (instead of a no treatment control group) is chosen to increase the likelihood of continued study participation by guaranteeing that all participants receive treatment. Furthermore, the inclusion of a waiting list control group allows a treatment versus no treatment comparison that will provide knowledge about the effects of treatment relative to natural recovery from loss.

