### Statistical analyses

To examine the differences in reductions of symptom levels of PCBD, PTSD and depression from pretreatment to post-treatment/waiting period between the conditions (online CBT vs waitlist), three independent multilevel models will be built (hypothesis 1). Symptom levels of PCBD, PTSD, and depression will consecutively be included as dependent variables and condition (online CBT vs waitlist controls), time and time × condition (interaction term) as predictor variables, taking into account that repeated observations (level 1) are nested within individuals (level 2), and within households (level 3; if applicable). Additionally, relevant background, loss-related variables and use of cointerventions (yes/no) during participation in our study will be included in the analysis as covariates. Deviance tests will be used to examine whether inclusion of these covariates improves model fit.^57^ Data of all participants entering the study will be included in all analyses (ie, intention-to-treat analysis). Furthermore, percentages of people meeting diagnostic criteria for PCBD, PTSD and clinically relevant depression will be calculated for each measurement occasion and percentages of people reporting reliable change scores for each outcome measure, using a formula from Jacobson and Truax,^58^
^p 14^ will be reported.

To examine to what extent symptom improvement after treatment is related to improvement in possible correlates of change, residual gain scores will be calculated for all outcome measures (ie, PCBD, PTSD and depression) and possible correlates of change (ie, negative cognitions, avoidance behaviours, state anger, a sense of unrealness and self-efficacy). Following previous research^59^, residual gain scores will be calculated by subtracting the standardised combined pretreatment scores of both conditions (T1 data from immediate treatment condition and T1b data from waitlist condition) multiplied by the correlation coefficient between standardised combined pretreatment scores and standardised post-treatment (or follow-up) scores from standardised post-treatment (or follow-up) scores. To test hypothesis 2a, multiple regression analyses will be conducted to examine the associations between residual gain scores of PCBD, PTSD or depression and residual gain scores of negative cognitions, avoidance behaviours, state anger, a sense of unrealness and self-efficacy.

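### As worded, the co-intervention question misses the waitlist arm's 20-week wait, although the hypothesis 1 models use outside care as a covariate

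*Protocol article*

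**What the plan says.** - **Outside care is permitted.** Protocol article, Other measures: "Participants are allowed to receive other forms of psychosocial, instrumental or legal support during participation in the trial".
- **How it is recorded.** The same section gives a single question and names its occasions and look-back periods: "During the past 12 weeks/8 weeks (for T2 and T3, respectively) did you receive additional psychological professional support". It asks about care additional to the study's own online therapist. Two further items at T1 ask about support received before entry.
- **What the occasions mean.** The Design section labels them differently by arm. The first post-allocation assessment is at "12 weeks postallocation (T2 for the intervention condition and T1a for waitlist controls" and the second at "20 weeks postallocation (T3 for the intervention condition and T1b for waitlist controls". Waitlist participants start CBT after the 20-week wait, and "they will be asked to fill in T2 and T3 12 and 20 weeks after starting treatment, respectively".
- **How the variable is used.** In the models for hypothesis 1, according to Statistical analyses, "use of cointerventions (yes/no) during participation in our study will be included in the analysis as covariates". Deviance tests then examine whether the covariates improve fit.
- **How the control is described.** The Design section says that the waitlist allows a comparison with no treatment that will "provide knowledge about the effects of treatment relative to natural recovery from loss".

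**The concern.** The question is tied to T2 and T3, and these labels refer to different calendar periods in the two arms. In the CBT arm they span the randomised comparison. In the waitlist arm they fall after crossover. Read as it stands, the plan records outside care during the comparison for one arm only.

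Two things are at stake. First, the hypothesis 1 covariate has no usable value for controls. It is either absent over the window of interest, or filled from a later period in which controls are themselves receiving CBT. In the second case the same variable would mean different things in the two arms. Second, the control is presented as showing natural recovery, yet controls may see a psychologist elsewhere while they wait. The data as described could not show whether they did.

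The point is when the item is asked. Whether a post-randomisation variable belongs in the model at all is a separate question.

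**Working it through.** The plan states no figure on this point that could be reproduced. The check places each look-back window on an axis of weeks since allocation.

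**Inputs**
- Design: in the CBT arm, T2 is at week 12 and T3 at week 20.
- Design: in the waitlist arm, T1a is at week 12 and T1b at week 20; T2 and T3 are 12 and 20 weeks after CBT starts.
- Other measures: the look-back is 12 weeks at T2 and 8 weeks at T3.
- Assumption: waitlist CBT starts at week 20, directly after the wait.

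**Formula.** With start week s (0 for CBT, 20 for waitlist), T2 = s + 12 and its window runs from s to s + 12. T3 = s + 20 and its window runs from s + 12 to s + 20. The overlap is counted against the randomised period, weeks 0-20.

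| Arm | T2 | T2 window | T3 | T3 window | Randomised weeks covered |
|---|---|---|---|---|---|
| CBT (s = 0) | 0 + 12 = 12 | 0-12 | 0 + 20 = 20 | 12-20 | 12 + 8 = 20 of 20 |
| Waitlist (s = 20) | 20 + 12 = 32 | 20-32 | 20 + 20 = 40 | 32-40 | 0 + 0 = 0 of 20 |

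The result does not depend on an exact start. If waitlist CBT begins d weeks late, the windows move to 20 + d to 32 + d and 32 + d to 40 + d, and the overlap with weeks 0-20 stays at 0.

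**With the item also asked at T1a and T1b.** The T1a window is weeks 0-12 and the T1b window is weeks 12-20, so the waitlist arm is covered for 12 + 8 = 20 of 20 weeks.

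**Is the labelling merely loose?** Elsewhere it is used strictly. For the residual gain scores, Statistical analyses takes T1 as the pretreatment score in the immediate-treatment arm and T1b in the waitlist arm. The reference to care beyond the study's online therapist also suits someone already in treatment better than someone still waiting, who has no study therapist.

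**Do the T1 items fill the gap?** They ask whether support was ever received before participation. The loss-related item would catch care already under way at entry, but cannot separate it from care that has ended. Neither item can record care begun during the wait.

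**The case against.** The strongest reply is that recording during the wait may well be intended.

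- The Design section says "All participants will be asked to fill in questionnaires (described below) at baseline (T1" and at both post-allocation assessments, and the co-intervention question is among the measures described there.
- The covariate is defined over participation in the study, which presupposes data from controls during the wait.
- The 12- and 8-week look-backs fit T1a and T1b exactly, so T2 and T3 could be shorthand for the 12- and 20-week assessments in either arm.
- A condensed article often leaves the item-by-occasion schedule to the full protocol.

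Much of this stands as evidence of intent. It does not settle the text. The general sentence about questionnaires cannot mean every item at every occasion: the alliance scale is given after session 4, and the prior-support items belong to T1. Nor is this simply a detail left out, because the article states the occasions and look-backs, and what it states does not supply the covariate that it later needs.

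A reader might go further in three ways that the document does not support:

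- *That outside care during the wait will never be recorded.* The article does not exclude asking at T1a and T1b. It only fails to say so.
- *That the trial's main contrast falls.* It does not. The intention-to-treat comparison of online CBT with a waitlist, with outside care allowed in both arms, is valid without this variable.
- *That the CBT effect is diluted by some definite amount.* The document gives no rate of outside care in either arm and no effect for it. Dilution would depend on the difference in uptake between the arms, which could be small, and any percentage would be pure assumption.

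**Conclusion.** The point holds in a limited form. As written, the question covers 20 of 20 randomised weeks in the CBT arm and 0 of 20 in the waitlist arm. This rests on taking the Design section's labels at face value, as the Statistical analyses section itself does. Two consequences follow:

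- **Covariate.** For controls, the hypothesis 1 covariate is missing or is measured after the randomised contrast has ended. If it is missing, a model that needs it would, under ordinary handling of missing covariates, lose control participants, against the stated inclusion of everyone who enters the study. If it is taken from weeks 20-40, it follows the outcomes it is meant to explain and may reflect how controls responded to CBT.
- **Interpretation.** The description of the waitlist as no treatment or natural recovery cannot be checked from the data described.

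The randomised comparison is unaffected. If asking at T1a and T1b was always intended, the defect is one of wording, but it still needs correcting, because the text as it stands directs otherwise. It should be fixed, and the fix is cheap.

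**What to change.** 1. In Other measures, state that waitlist participants answer the same question at T1a (past 12 weeks) and T1b (past 8 weeks), as well as at their T2 and T3. The reference to the study's online therapist can be dropped for people still waiting.
2. In Statistical analyses, define the hypothesis 1 co-intervention covariate over weeks 0-20 after allocation in both arms, from T2 and T3 in the CBT arm and from T1a and T1b in the waitlist arm.
3. Report outside psychological care by arm for weeks 0-20 next to the hypothesis 1 result.
4. If the waiting-period data are not collected, describe the control as a waitlist with outside care allowed, and drop the language of no treatment and natural recovery.

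The cost is one short existing item on two online questionnaires that are already sent. The sample size does not change and no visit is added. The article says that recruitment had not begun at submission, so the item could be placed before the first participant reached T1a. Collecting the information later would depend on longer recall.

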### Statistical analyses

To examine the differences in reductions of symptom levels of PCBD, PTSD and depression from pretreatment to post-treatment/waiting period between the conditions (online CBT vs waitlist), three independent multilevel models will be built (hypothesis 1). Symptom levels of PCBD, PTSD, and depression will consecutively be included as dependent variables and condition (online CBT vs waitlist controls), time and time × condition (interaction term) as predictor variables, taking into account that repeated observations (level 1) are nested within individuals (level 2), and within households (level 3; if applicable). Additionally, relevant background, loss-related variables and use of cointerventions (yes/no) during participation in our study will be included in the analysis as covariates. Deviance tests will be used to examine whether inclusion of these covariates improves model fit.^57^ Data of all participants entering the study will be included in all analyses (ie, intention-to-treat analysis). Furthermore, percentages of people meeting diagnostic criteria for PCBD, PTSD and clinically relevant depression will be calculated for each measurement occasion and percentages of people reporting reliable change scores for each outcome measure, using a formula from Jacobson and Truax,^58^
^p 14^ will be reported.

To examine to what extent symptom improvement after treatment is related to improvement in possible correlates of change, residual gain scores will be calculated for all outcome measures (ie, PCBD, PTSD and depression) and possible correlates of change (ie, negative cognitions, avoidance behaviours, state anger, a sense of unrealness and self-efficacy). Following previous research^59^, residual gain scores will be calculated by subtracting the standardised combined pretreatment scores of both conditions (T1 data from immediate treatment condition and T1b data from waitlist condition) multiplied by the correlation coefficient between standardised combined pretreatment scores and standardised post-treatment (or follow-up) scores from standardised post-treatment (or follow-up) scores. To test hypothesis 2a, multiple regression analyses will be conducted to examine the associations between residual gain scores of PCBD, PTSD or depression and residual gain scores of negative cognitions, avoidance behaviours, state anger, a sense of unrealness and self-efficacy.

To achieve research aim 2b, multiple regression analyses will be used to examine to what extent residual gain scores of PCBD, PTSD and depression varies as function of a) background characteristics, including gender (male/female), age (in years) and educational level (low/high), kinship to the deceased (child/spouse vs other) and time since loss (in years) and b) accident-related stressors, including number of losses (single vs multiple), witnessing the accident (yes/no) and status of legal trial (not applicable/ongoing/completed). Condition (intervention vs waitlist controls) will be added as a covariate to fulfil research aims 2a and 2b.

To achieve the third research aim: (1) differences in therapeutic alliance scores will be assessed between people who completed and dropped out of treatment and (2) multiple regression analyses will be used to examine to what extent symptom improvement in PCBD, PTSD and depression is related to therapeutic alliance (from both participant and therapist perspectives).

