### Sample size

To test our primary hypothesis (hypothesis 1), a test for each outcome separately (PCBD, PTSD and depression) will be conducted to assess the effects of online CBT versus waitlist controls. To find a difference between two groups (online CBT vs waitlist controls) of at least a medium effect size (f=0.25; based on prior research^22 28 40^) with a power of 80%, an α of 0.017 (corrected for multiple testing, that is, 0.05/3, as there are three primary outcome measures (PCBD, PTSD and depression), and a strong association (r=0.50) between the preassessment and postassessment, a sample size of 23 per condition is sufficient. Taking into account an average dropout rate of 19%,^22^ a total sample size of 55 (46+9) is required to test hypothesis 1.

Because our data are nested (repeated measures) (level 1) within individuals (level 2), and possibly within families sharing the same household (level 3), multi-evel modelling will be performed to test hypothesis 1. Conducting a power analysis within a multilevel framework is not feasible for various reasons.^42^ Our power analysis is therefore based on a repeated measures analysis of variance.

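### Free improvement: the hypothesis 1 model lets the randomised arms differ at baseline, so it tests change scores and makes inefficient use of the baseline measurement (an efficiency loss, not bias)

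*Protocol article*

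**What the plan says.** The Statistical analyses section sets the target of hypothesis 1 as "differences in reductions of symptom levels of PCBD, PTSD and depression from pretreatment to post-treatment/waiting period between the conditions". Each of the three symptom scores is the dependent variable in its own multilevel model, with "condition (online CBT vs waitlist controls), time and time × condition (interaction term) as predictor variables". Observations are nested in persons and, where applicable, in households.

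On further covariates it says that "relevant background, loss-related variables and use of cointerventions (yes/no) during participation in our study will be included in the analysis as covariates", with deviance tests to judge whether they improve fit. The baseline symptom score is not in that list, and no common baseline mean is stated.

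The Sample size section assumes "at least a medium effect size (f=0.25" (f=0.25), "with a power of 80%, an α of 0.017", and "a strong association (r=0.50) between the preassessment and postassessment", and concludes that "a sample size of 23 per condition is sufficient". It adds: "Our power analysis is therefore based on a repeated measures analysis of variance".

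**The concern.** When baseline is one of the outcome rows and condition has its own main effect, the model estimates a separate baseline mean for each arm. The time × condition term is then the arm difference in follow-up means minus the arm difference in baseline means, which is a change-score contrast. In a randomised trial the second part has expectation zero. Subtracting it in full adds noise whenever the baseline-to-follow-up correlation is below 1.

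Two things follow:

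- **Precision.** The contrast is less precise than the data already collected would allow, in a small trial whose alpha is split over three outcomes.
- **Chance imbalance.** Full subtraction over-corrects for an accidental baseline difference when r<1. A common-baseline model corrects only by the amount that the correlation supports.

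**Working it through.** **Inputs.** From Sample size: f=0.25, alpha 0.017, power 80%, r=0.50, 23 per arm (N=46). From Design: 1:1 random allocation, with measurements at baseline, 12 and 20 weeks. Sidedness is not stated; the F test used here is equivalent to a two-sided t test.

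**1. The plan's own figure.** Take the within-between interaction of a repeated-measures ANOVA with 2 groups and m=2 occasions. The noncentrality is λ = f²·N·m/(1−r), with 1 and N−2 degrees of freedom.
- N=46: λ = 0.0625 × 46 × 2 / 0.5 = 11.5, power 81.4%.
- N=44: power 79.3%.
- The smallest sufficient N is 45, which becomes 46 with equal arms. The plan's 23 per condition is reproduced.
- Other readings do not reproduce it. The between-group test needs 128 (two occasions) or 116 (three occasions). The interaction with three occasions needs 36.

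The sample size was therefore computed for the two-occasion change-score contrast.

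**2. What f=0.25 means on this contrast.** For a difference in change of δ SD, λ = δ² / [2(1−r) × 4/N]. With δ=1.0, r=0.50 and N=46 this is 1 / (1.00 × 4/46) = 11.5, the same λ as in step 1. So f=0.25 corresponds to δ = 4f = 1.0 SD.

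**3. Variance of the two contrasts** (n per arm, outcome SD σ, one follow-up visit).
- Free baseline means: 2σ²(1−r) × 2/n. The unit factor at r=0.50 is 2 × 0.5 = 1.00.
- Common baseline mean: σ²(1−r²) × 2/n. The unit factor at r=0.50 is 1 − 0.25 = 0.75.
- Ratio: (1−r²) / [2(1−r)] = (1+r)/2 = 0.75. The standard-error ratio is √0.75 = 0.866, so the confidence interval is about 13% narrower.

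**4. Dependence on r.** Only r=0.50 is the plan's; the other values are an assumed range.

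| r | variance ratio | reduction |
|---|---|---|
| 0.3 | 0.65 | 35% |
| 0.4 | 0.70 | 30% |
| 0.5 | 0.75 | 25% |
| 0.6 | 0.80 | 20% |
| 0.7 | 0.85 | 15% |
| 0.8 | 0.90 | 10% |

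The direction is the same for every r<1; only the size changes.

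**5. Dependence on time coding.** With three occasions, a random-intercept covariance and r=0.50, the reduction is 25% for the 12-week or the 20-week contrast alone, 27-30% for a linear slope, and 33% for the average of both visits.

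**6. Power at N=46, alpha 0.017, r=0.50, complete data, one follow-up visit.** For the second column λ = δ² / (0.75 × 4/46), with one further degree of freedom spent on the baseline slope.

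| true difference in change | free baseline (as planned) | common baseline or baseline-adjusted |
|---|---|---|
| 1.0 SD | λ=11.5, 81% | λ=15.3, 92% |
| 0.8 SD | λ=7.36, 59% | λ=9.81, 74% |

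A simulation of 40,000 trials with 23 per arm and a 1.0 SD effect, using adjustment for the baseline score, gave a variance ratio of 0.755 and power of 81.3% against 91.3%. Both methods recovered the 1.0 SD difference without bias.

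**The case against.** The strongest reply is that nothing here is wrong. The hypothesis is worded as larger reductions, the model tests a difference in reductions, and the sample size was computed for that contrast. The three agree, and the test is valid under randomisation. All of this stands. A reader might infer from the lost precision that the trial is underpowered against its own target, or that the primary comparison is biased. The documents support neither: step 1 gives 81% at the planned number, and the planned contrast has the right expectation.

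A second reply is that a flat figure of one quarter is not fixed by the plan. That also stands. It rests on an assumed r and on a single-visit contrast, and the article does not say how time is coded. The size therefore has to be given as a range. The power figures assume two occasions and complete data, whereas the trial has three occasions and expects 19% dropout.

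A third reply is that this is detail for a fuller analysis plan. That carries less weight: the article names the model terms, and those terms imply free baseline means.

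Three further readings should be resisted:

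- **The plan ignores baseline imbalance.** It subtracts baseline in full; the valid point is only that this over-corrects when r<1.
- **Randomisation is unstratified.** The Design section describes blocking and is silent on strata.
- **Using baseline as a covariate for the follow-up scores is interchangeable with the constrained model.** A participant with no follow-up score contributes no outcome row to the covariate version, which does not fit the commitment to analyse everyone who enters the study.

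**Conclusion.** The point holds as a nearly free gain in efficiency and not as an error. The planned test is valid and powered as stated. With a common baseline mean, the same participants and measurements would give a single-visit contrast with 25% less variance at the plan's r=0.50, and 35% to 10% less over an assumed r of 0.3 to 0.8. At 23 per arm with complete data, power rises from 81% to about 91-92% for a 1.0 SD difference in change. The gain is worth most if the true effect is below the 1.0 SD that f=0.25 implies on this contrast: at 0.8 SD, power is 59% as planned and 74% with the constraint. The conclusion rests on random allocation, similar variances at baseline and follow-up, and the planned correlation.

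**What to change.** Before outcomes are analysed by arm, amend the hypothesis 1 paragraph of Statistical analyses to specify a constrained longitudinal multilevel model for each outcome:

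- time as a categorical factor with baseline as the reference;
- time × condition terms at 12 and 20 weeks, and no condition difference at baseline;
- the person level as planned, and the household level if applicable;
- a small-sample degrees-of-freedom correction.

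Prefer this to modelling only the follow-up scores with baseline as a covariate, because it keeps participants who have a baseline score but no follow-up, as the intention-to-treat statement requires.

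The cost is small: a little more model specification and, if an unstructured within-person covariance is chosen, a few more covariance parameters to estimate with about 55 participants. No change to recruitment, measurements or sample size is needed.
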